In a healthcare system with fixed capacity even a small saving in length of stay can be important. The Australasian College for Emergency Medicine recently reported that if a hospital with 20,000 admissions each year saved half a bed day per patient by improving discharges, about 2000 extra patients a year could be admitted [29]. Data from our pilot study suggests that if the average length of stay from each rehabilitation episode was reduced by 3.2 days, there would be an additional 68 patients admitted to a typical 30-bed rehabilitation facility each year [28]. These results have the potential to increase patient flow from the acute to the subacute setting providing increased capacity in the acute care setting. A rigorous health economic evaluation in a larger trial is required to confirm the cost effectiveness of providing additional allied health services for rehabilitation.

In summary, to evaluate the potential benefits of the provision of additional Saturday allied health services to rehabilitation inpatients, we will conduct a fully powered randomized controlled clinical trial that will: complete an economic analysis of additional allied health services compared with the traditional Monday to Friday usual care service from a healthcare system perspective; and incorporate occupational therapy rehabilitation services in addition to physiotherapy.

The primary aim of this trial is to determine if the provision of additional Saturday allied health services will reduce the costs of care by reducing patient rehabilitation length of stay without affecting health related quality of life and functional outcomes compared to those receiving usual care. The secondary aims are to examine if the provision of additional Saturday allied health services has any effect on therapeutic functional goals at discharge; or the use of community-based health services post discharge from the sub-acute hospital setting, compared to those receiving usual care. For the purpose of this clinical trial the term "allied health" will specifically refer to physiotherapy and occupational therapy services.

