### Primary outcomes measures

Patient length of stay will be measured as the number of overnight stays in the rehabilitation unit, from the day of admission until the day of discharge from the unit. Length of stay is the largest contributor of direct care costs during rehabilitation [32,33].

The EuroQol questionnaire (EQ-5D) and the EQ-VAS [34] will be used to measure the participant's quality of life, covering the domains of mobility, self-care, usual activities, pain/discomfort, and anxiety/depression, and overall health state (EQ-VAS). The EQ-5 D is a standardised instrument for measuring health related quality of life and providing a single index of utility, necessary for the calculation of a cost utility ratio in an economic analysis. It has been used for a range of conditions and changes in the EQ-5 D are significantly correlated with changes in condition-specific measures over three months (*p*= 0.01) [35].

The Functional Independence Measure (FIM) [36] will be used to assess the amount of assistance required to complete activities including feeding, dressing, transfers, walking, stairs, and cognitive function. The FIM has demonstrated strong psychometric qualities in rehabilitation settings with high levels of reliability (ICC = .96) [37] and evidence for responsiveness and validity as a global disability measure for patients receiving rehabilitation [38].

Follow-up measures of the FIM and EuroQol at 6 and 12 months will be collected by telephone by assessors blinded to group allocation. There is evidence that telephone administration is a valid method of assessing functional status in older patients after rehabilitation [39].

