### Secondary outcome measures

Secondary outcomes measures include the 10 metre walk test [40], the timed up and go test [41], and the Personal Care Participation Assessment and Resource Tool (PC-PART) [42]. The modified motor assessment scale [43] will be completed on patients with a neurological diagnosis. All secondary outcome measures are designed to evaluate clinical outcomes relevant to the functional goals of therapy, and will be measured on admission and at discharge.

Discharge destination will be recorded as home, high level residential care, low level residential care, and acute hospital transfer. This will be recorded as "worse" when the participant was discharged to a destination where more assistance would be provided, for example a high level residential care facility, or "same" when a participant was discharged to the same place of accommodation prior to the hospital admission. This outcome measure is included to measure any increase in burden of care to the community.

Demographic data on participant age, gender and co-morbidities will be documented from each participant's medical chart. Co-morbidities will be recorded using the Charlson co-morbidity index [44].

Adverse events, including falls, nosocomial infections and mortality will be recorded on an incident report form through an audit of participants at discharge and the rehabilitation facilities' incident reporting database. Follow-up physiotherapy and occupational therapy will be recorded at discharge as outpatient, community rehabilitation (including centre-based and home services), or no follow up.

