### Statistical analysis

Between group differences of the primary outcomes (length of stay, EuroQol, and FIM) will be analysed with analysis of covariance of discharge scores with the baselines score as covariate [45]. Intention to treat analysis will be used with any missing health outcome data imputed using the last value carry forward method [46].

A rigorous economic evaluation will be carried out alongside the randomised clinical trial. Cost effectiveness of the intervention will be determined as the incremental cost of additional Saturday allied health inpatient rehabilitation services compared to usual inpatient rehabilitation per quality adjusted life year saved. The primary measure of incremental effect for the economic evaluation will include the difference in health related quality of life between the control and treatment groups using the EuroQol. A secondary incremental cost effectiveness ratio will be determined using the cost per change in functional status using the FIM.

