Patient level costing and utilisation data for inpatient rehabilitation services from the hospital's costing and admission and discharge system will be used to estimate the costs of inpatient care. Following discharge, the patient health service utilisation questionnaire will be administered at 6 and 12 months to determine the health care services used post discharge. Costs will be attributed to these services based on published costing data from the National Hospital Cost Data Collection, Medicare Australia, and the Pharmaceutical Benefits Scheme. Where a patient is re-admitted to one of the participating rehabilitation facilities within the 12-month period inpatient costing data will be used. Medicare Australia data will be used to obtain private health service utilisation. The costs of implementing the intervention (Monday to Saturday rehabilitation) and the control programs (Monday to Friday rehabilitation) will be determined from the rehabilitation facility. This will include therapist time, equipment, consumables and administrative overheads. The incremental cost estimate will be determined as the difference in cost of implementing the Saturday allied health rehabilitation service plus the difference in health service costs (including out-of-pocket private expenditure) used in the 12 months post discharge between the control and intervention groups. A secondary incremental cost estimated will be calculated as the change in resource use resulting from the additional Saturday allied health rehabilitation service compared to usual Monday to Friday rehabilitation at the point of discharge from the inpatient rehabilitation facility. Any missing health service utilisation or cost data, where service use was recorded but a quantity not specified, will be imputed using within group mean cost [47].

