The primary health economic analysis is a cost utility analysis from a health care system perspective, with outcomes based on health related quality of life (using EuroQol), and cost effectiveness using an intermediate clinical outcome (based on the FIM). We will be undertaking an intention to treat analysis where the cost utility ratio will be calculated as the change in total program and health service cost per change in quality adjusted life year saved in the intervention and control groups at 6 and 12 months. Additional cost effectiveness ratios will be calculated as the total program cost per 10% change in functional independence (at discharge), and the total program and health service cost per 10% change in functional status between the control and intervention groups over a 12 month period. One way sensitivity analysis will be undertaken to investigate the robustness of the cost effectiveness ratio to a range of cost and effect estimates, including alternative delivery arrangements, wage rates and program length on the cost side, and health related quality of life and FIM on the effect side.

Between group differences of secondary outcomes measured on continuous or ordinal scales will be analysed with analysis of covariance of discharge scores with the baselines score as covariate [45]. Between-group differences in discharge destination (home versus other) will be analysed with relative risk ratios.

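### Last value carried forward, as the only rule for missing FIM and EQ-5D, biases the discharge comparison: towards no difference if missingness is similar in both arms, in either direction if it is not

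*Protocol article*

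**What the plan says.** The rule in the Statistical analysis section is: "Intention to treat analysis will be used with any missing health outcome data imputed using the last value carry forward method". It has no exception and no alternative. In the same section, the primary outcomes (length of stay, EuroQol and FIM) "will be analysed with analysis of covariance of discharge scores with the baselines score as covariate". FIM and EuroQol are measured at admission and discharge, and then: "Follow-up measures of the FIM and EuroQol at 6 and 12 months will be collected by telephone by assessors blinded to group allocation" (Primary outcomes measures).

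Three other statements bear on the rule:

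- The primary aim in the Background is to lower costs through a shorter stay "without affecting health related quality of life and functional outcomes compared to those receiving usual care".
- EuroQol feeds the main economic result, an intention-to-treat ratio at 6 and 12 months of the "change in total program and health service cost per change in quality adjusted life year saved in the intervention and control groups" (Statistical analysis).
- Deaths are anticipated: "Adverse events, including falls, nosocomial infections and mortality will be recorded on an incident report form" (Secondary outcome measures). No rule is given for FIM or utility after death.

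The only sensitivity analysis described is one-way, on the cost-effectiveness ratio. It varies quality of life and FIM as inputs, but it is not presented as a test of the missing-data assumption.

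**The concern.** Inpatient rehabilitation is meant to produce gains between admission and discharge. Someone without a discharge score has only an admission score to carry forward, so the rule enters a gain of exactly zero. For a missing 6- or 12-month score the assumption is different: no change since discharge, or since 6 months.

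Missing scores are foreseeable, and they are unlikely to be a random subset. The article lists transfer back to acute care as a discharge destination and records mortality. It enrols people with cognitive impairment (24% severe in the pilot) and relies on telephone follow-up to 12 months.

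What is at stake is the claim that a shorter stay does not cost patients function or quality of life. By randomisation, admission values have the same expectation in both arms, so filling gaps with them dilutes any real discharge difference. For a trial that hopes to report no deterioration, dilution is the unsafe direction. The Background already reads the pilot's non-significant differences as evidence that care was not harmed. If one arm has more missing scores than the other, the zero gains are unevenly spread and produce a difference that has nothing to do with treatment.

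**Working it through.** **The plan's own figure.** The sample size section gives 356 per group for an effect size of 0.21 and power 0.80. Taking alpha as 0.05 two-sided (not stated), the two-means formula returns 356 and power 0.800. That figure is not in dispute. It supplies the group size and a reference effect for the check.

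**Inputs.** From the article: 356 per arm, ANCOVA on the admission score, carry-forward for any missing value. Assumed, because the article gives none: missing share 10% to 30%, mean gain in the control arm G = 0.5 or 1 SD, true harm D = −0.21 SD (borrowing the planned effect size), correlation between admission and discharge 0.6, missingness unrelated to outcome.

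**Formula at discharge.** With missing shares m_int and m_ctl, and gain counted as zero when missing:

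expected difference = (1 − m_int)(G + D) − (1 − m_ctl)G = (1 − m_int)D − (m_int − m_ctl)G.

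*Similar missingness (m in both arms).* The second term vanishes and (1 − m)D remains:

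- 10%: 0.90 × (−0.21) = −0.189
- 20%: 0.80 × (−0.21) = −0.168
- 30%: 0.70 × (−0.21) = −0.147

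*Unequal missingness, G = 1 SD.*

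- 15% intervention, 5% control: 0.85 × (−0.21) − 0.10 × 1 = −0.279; harm is exaggerated.
- 5% intervention, 15% control: 0.95 × (−0.21) + 0.10 × 1 = −0.100; harm is more than halved.
- No true effect (D = 0): the 10-point imbalance alone gives a difference of 0.10 SD, its sign depending on which arm has more missing. With G = 0.5 SD it is 0.05 SD.

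**Simulation.** ANCOVA, 356 per arm, 2,000 runs per setting, G = 1 SD:

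| True D | Missing int / ctl | Carry-forward: mean, rejection rate | Available cases: mean, rejection rate |
|---|---|---|---|
| −0.21 | 0 / 0 | −0.21, 93% | −0.21, 93% |
| −0.21 | 10% / 10% | −0.19, 87% | −0.21, 92% |
| −0.21 | 20% / 20% | −0.17, 78% | −0.21, 87% |
| −0.21 | 30% / 30% | −0.15, 69% | −0.21, 84% |
| −0.21 | 5% / 15% | −0.10, 38% | −0.21, 93% |
| 0 | 15% / 5% | −0.10, 38% | 0.00, 5% |
| 0 | 5% / 15% | 0.10, 37% | 0.00, 4% |

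With G = 0.5 SD the false-positive rate under the same 10-point imbalance is about 14%. The simulation agrees with the formula. It also shows that carry-forward adds bias in a setting where leaving out the missing patients would add none.

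**Deaths, if the rule is applied literally.** Assume utility 0.5 to 0.7 and death on average mid-year. Each death is then credited 0.5 × 0.5 = 0.25 to 0.7 × 0.5 = 0.35 QALY that was not lived. If 5% died in one arm and 8% in the other, the true QALY difference due to deaths, 0.03 × 0.25 = 0.0075 to 0.03 × 0.35 = 0.0105 per patient, would disappear.

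**The case against.** Several points on the other side have force.

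*Follow-up data behave differently.* At 6 and 12 months the carried value usually keeps the inpatient gain and any effect already visible at discharge. The (1 − m) shrinkage is derived for carried-forward admission scores and does not transfer to later scores or to QALYs. This stands.

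*The direction is not fixed.* A reader might infer that the rule always pulls towards no harm. It does so only when missingness is similar in both arms; more missing in the intervention arm can exaggerate or create harm. The Abstract also asks whether Saturday therapy improves health, and for that question shrinkage is conservative. Both points stand.

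*Deaths.* A reader might infer that the plan credits the dead with quality of life. The article does not say that a score after death counts as missing, and a fuller plan could set utility to zero. The credit follows only from a literal reading of the rule, so it calls for a clarifying sentence and is not an established error.

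*Interval width.* A reader might infer that carry-forward makes confidence intervals too narrow in general. That is not shown. With equal random missingness of 10% to 20% and no effect, the type I error was 4.6% to 5.1%. At an assumed gain of 1.5 SD and 20% missing, the carry-forward standard error was larger than the available-case one (0.071 against 0.067). The demonstrated fault is bias.

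*Costs.* A reader might extend the criticism to cost gaps, which "will be imputed using within group mean cost". The article confines that rule to entries where a service was reported without its amount. It is an item-level matter outside this point.

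*Length of stay.* It drives the sample size, comes from admission and discharge records, and is little affected. True, but FIM and EuroQol are also named primary outcomes, and EuroQol carries the cost-utility result.

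None of this rescues carry-forward as the sole method. The article states the rule outright, so this is not a detail left for a later document.

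**Conclusion.** The concern holds for FIM and EQ-5D. Carry-forward is fixed as the only method, it assumes no inpatient gain for a missing discharge score and no further change for a missing later score, and no missing-data sensitivity analysis is described. With similar missingness the discharge difference is reduced by roughly the fraction missing: a true −0.21 SD becomes −0.19 to −0.15 SD at 10% to 30% missing. With unequal missingness the added bias is the difference in missing shares times the mean gain. A 10-point imbalance gives 0.05 to 0.10 SD for an assumed gain of 0.5 to 1 SD, and a false-positive rate of about 14% to 38% when there is no effect.

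These sizes rest on assumed missing rates, gains and correlation, and on missingness unrelated to outcome. The article supplies none of these, and no mortality figure. If few discharge scores are missing and the arms are balanced, the effect will be small. The form of the bias does not depend on these figures, and the rule should be changed before the analysis.

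**What to change.** In the Statistical analysis section, replace carry-forward as the primary method:

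1. **FIM and EQ-5D.** Use a likelihood-based repeated-measures model with the admission score as covariate and discharge, 6 and 12 months as outcomes. Alternatively, use multiple imputation by arm with collected baseline variables (admission FIM and EQ-5D, site, case-mix stratum, age, co-morbidity).
2. **QALYs.** Use multiple imputation for missing utilities.
3. **Deaths.** State that carry-forward does not apply after death and that utility is 0 from the date of death. Report FIM among survivors alongside deaths by arm.
4. **Sensitivity.** Keep carry-forward as a sensitivity analysis only, and add a delta-adjusted scenario for data missing not at random.

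The cost is a change of wording and modest extra programming. One item goes beyond analysis: the article describes mortality capture only through a discharge audit and the facilities' incident database. Deaths after discharge, with dates, would have to be established through the 6- and 12-month contacts already planned.

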## Discussion

This paper outlines the study protocol for the first fully powered prospective randomised clinical trial to establish if additional Saturday allied health services to rehabilitation inpatients reduces length of stay without compromising discharge outcomes. An economic analysis will determine the cost effectiveness of providing additional allied health services.

If successful this project will have substantial health benefits for the patient, the health care system, and for the organisation delivering health services, especially in the sub-acute sector. Increasing capacity in the sub-acute sector will have considerable flow-on effects into the acute health care sector. The results of this project will be applicable to the more than 18,000 patients receiving episodes of rehabilitation care in the public health system in Australia each year [48]. Based on the average length of stay in rehabilitation in the public system in Australia of 26.7 days [48], reductions of length of stay observed in our pilot project of about 3 days if confirmed in the proposed trial have the potential to save more than $40 M, and would allow more than 2,200 extra patients to receive rehabilitation each year across Australia. Our economic evaluation analysis will allow a rigorous evaluation of the potential benefits of providing additional rehabilitation and include health care costs other than length of stay and take into account functional outcomes and quality of life after discharge.

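### The stated incremental cost formula has no explicit term for the index rehabilitation stay, which does not fit the trial's aim of saving cost through a shorter stay

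*Protocol article*

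**What the plan says.** All of this is in the protocol article.

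- **Background, primary aim.** The trial asks whether the Saturday service "will reduce the costs of care by reducing patient rehabilitation length of stay" without harm to quality of life or function.
- **Primary outcomes measures.** Length of stay is described as the biggest driver of direct care cost in rehabilitation. Inpatient care is the first source named for the cost outcome.
- **Statistical analysis, inpatient costing.** Patient-level hospital data "will be used to estimate the costs of inpatient care".
- **Statistical analysis, implementation cost.** Of the cost of running the two programs, the article says: "This will include therapist time, equipment, consumables and administrative overheads".
- **Statistical analysis, formula.** The incremental cost has two parts: "difference in cost of implementing the Saturday allied health rehabilitation service plus the difference in health service costs (including out-of-pocket private expenditure"). The second part counts only what is "used in the 12 months post discharge between the control and intervention groups".
- **Statistical analysis, secondary estimate.** A second incremental cost, labelled secondary, is the change in resource use up to discharge from the rehabilitation facility.
- **Statistical analysis, ratios.** The primary cost-utility numerator is the change in program plus health service cost, with no post-discharge limit in that sentence. The ratio at discharge is the "total program cost per 10% change in functional independence (at discharge").
- **Discussion.** A reduction of about 3 days is said to "have the potential to save more than $40 M" nationally. The evaluation is also said to take in costs beyond those of the stay.

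**The concern.** The formula is the only place where the article spells out how the incremental cost is built. It has two parts: what the Saturday service costs to run, and what patients use after they leave. The ward cost of the rehabilitation admission is named in neither, although that is where a shorter stay would save money.

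An analyst who followed the sentence literally would enter the cost of the intervention, and any cost shifted to services after discharge, but not the bed-days saved in exchange. That error runs in one direction, against the intervention, and it would fall on the primary economic result. Index-stay resources would then fit naturally only in the estimate labelled secondary.

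**Working it through.** **1. Is the index stay in the formula?**

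| Cost item | Term 1: implementing the Saturday service | Term 2: health services used |
|---|---|---|
| Saturday therapist time, equipment, consumables, overheads | named | no |
| Ward and bed-day cost of the index stay | not named | outside the time window |
| Care in the 12 months after discharge | no | named |

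Read literally, the middle row is empty.

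**2. Do the ratios settle it?** The primary numerator combines program cost and health service cost. Those two labels match the formula's two terms. The ratio at discharge uses program cost alone, and the 12-month functional ratio adds health service cost back. That pattern suggests that health service cost means post-discharge cost. Program cost would then have to carry the ward cost, yet the description of program cost does not mention it. The wording does not exclude the broader reading, but it does not state it either.

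**3. Illustrative size.** The article gives no figure for the incremental cost, so its national projection is checked first and then used.

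Inputs:
- 18,000 episodes a year, average stay 26.7 days, reduction of about 3 days, saving of $40 M (Discussion; the episode count and the saving are both given as more than the stated amount).
- Pilot stays of 24.4 and 21.2 days (Background).
- One hour of physiotherapy and one of occupational therapy per Saturday (Intervention).
- Therapist cost of $50 to $150 per hour (assumption; the article gives none).

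Check of the article's projection:
- Bed-days freed: 18,000 × 3 = 54,000.
- Extra patients: 54,000 / (26.7 − 3) = 54,000 / 23.7 ≈ 2,278. This agrees with the article's figure of more than 2,200, so 54,000 bed-days is a reasonable base.

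Bed-day value:
- $40,000,000 / 54,000 ≈ $741 per day.
- At 3.0 days: 3.0 × $740.74 ≈ $2,222 per patient.
- Pilot difference: 24.4 − 21.2 = 3.2 days; 3.2 × $740.74 ≈ $2,370 per patient.
- If a bed-day is instead assumed to cost $400 to $1,000, then 3.2 days is $1,280 to $3,200.

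Saturday therapist time:
- 21.2 / 7 ≈ 3.03 Saturdays; × 2 h ≈ 6.06 h per patient.
- At $50 per hour: about $303. At $150 per hour: about $909.

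Incremental cost per patient, with post-discharge costs taken as equal:

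| Assumed hourly rate | Formula as worded | With 3.2 bed-days at $741 |
|---|---|---|
| $50 | +$303 | $303 − $2,370 ≈ −$2,068 (unrounded inputs) |
| $150 | +$909 | $909 − $2,370 ≈ −$1,462 (unrounded inputs) |

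Break-even hourly rate: $2,370 / 6.06 h ≈ $391.

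Break-even reduction in stay, with therapy held at 6.06 h and $741 per day: $303 / $741 ≈ 0.4 days at $50 per hour, and $909 / $741 ≈ 1.2 days at $150 per hour.

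**The case against.** A reader might infer that the bed-day saving cannot reach the primary cost-utility result, or that the trial is bound to report Saturday therapy as cost-increasing. The documents do not support either.

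- The primary numerator carries no post-discharge limit and takes a health care system perspective. An index admission can be read as a health service cost.
- The programs are described as Monday to Saturday and Monday to Friday rehabilitation, costed in both arms. The difference in implementation cost could therefore be a difference between whole inpatient programs. The list of components is not worded as exhaustive, and the sensitivity analysis varies program length on the cost side.
- Inpatient costs are to be collected and estimated, and the Discussion presupposes that the cost of the stay is counted. The discharge-point estimate could report the saving even on the narrow reading.
- The dollar figures are soft. The bed-day value divides one rounded lower bound by another, and the article does not say whether the $40 M is gross or net, or an average or marginal cost. The hourly rates are assumed and leave out equipment, consumables and overheads. The pilot interval for the 3.2 days ran from −0.5 to 6.9. Post-discharge costs could differ in either direction.

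All of this stands against the strong reading. It does not remove the inconsistency: these points show what the authors probably intended, while the one explicit formula says something narrower. Nor is this detail that a condensed article may leave out, because the article states the rule.

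**Conclusion.** The point holds as an inconsistency in a stated rule. The incremental cost formula has no explicit term for the index rehabilitation stay. That conflicts with the inpatient costing described in the same section and under the primary outcomes, with the broader cost-utility numerator, with the Discussion and with the primary aim.

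Applied literally, the formula would leave out about $2,200 to $2,400 per patient on the article's rounded figures, against about $300 to $900 of therapist time. That is enough to change the sign in this scenario. The scenario assumes a true reduction of 3.0 to 3.2 days, about $741 per bed-day, $50 to $150 per therapist hour, no other Saturday costs and equal post-discharge costs. The sign change is therefore an illustration of what the wording can do and not a prediction of the result. Because the wording can decide the direction of the primary economic finding, it should be settled before analysis.

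**What to change.** Define the primary incremental cost as the between-group difference in the sum of two parts:

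1. index inpatient rehabilitation cost from patient-level hospital costing, including bed-days, with Saturday therapy counted once; and
2. health service cost over the 12 months after discharge.

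Use that definition in the cost-utility numerator, and use the first part as the numerator of the ratio at discharge, so that one definition of cost runs through the section.

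This is a change of wording and needs no new data, since the inpatient costs are already to be obtained. The small cost is a check of the hospital costing extract: if it already contains therapy cost, the separately costed Saturday therapy must not be added a second time.
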